### Statistical Methods

Continuous variables will be presented as means, SDs, medians, and ranges. Categorical variables will be summarized with frequencies and percentages. When inferential analyses are conducted for continuous variables, they will be tested for normality. Nonparametric methods will be used for comparison of nonnormal data. Within-group comparisons will be done by using paired *t* tests, while between-group comparisons will be done using independent sample *t* tests for the data with normal distribution. Nonnormal data within the group will be compared using the Wilcoxon sign rank test, while between-group comparisons will be done by using the Mann-Whitney *U* test. Categorical data between groups will be compared using the *χ*^2^ or Fisher exact test. A 2-sided *P* value <.05 will be considered statistically significant. Per-protocol and intention-to-treat analyses will be carried out at the end of the study. All data will be analyzed using STATA 16.1 (StataCorp).

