### Outcome Measures

#### Primary Outcome Measure

The primary outcome measure is the mean change in the Control of Allergic Rhinitis and Asthma Test (CARAT) score [21] at baseline and days 16, 31, 45, 75, 105, and 135. The CARAT questionnaire comprises 10 questions about upper and lower airway symptoms, sleep interference, activity limitation, and the need to increase medication over a 4-week period (Multimedia Appendix 1, also available on the web [22]). The total possible score ranges from 0 (minimum control) to 30 (maximum control) [21].

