### Sample Size

In a previous pilot study on this Ayurvedic intervention, a change of 14 points in the CARAT score was observed. For this study, it was assumed that a change of 10 points would be seen in the placebo group. With an SD of 6 points based on the results of the previous pilot study, a sample size of 35 participants per group was calculated to provide 80% power, with a 95% CI.

Assuming a dropout rate of 20%, a total of 90 participants, 45 per group, will be included in this trial.

n_1_ = n_2_ = 2 *σ*^2^ [(Z_1 – α/2_) + (Z_β_)]^2^ ÷ Δ^2^

n_1_ = n_2_ = 2 * (6)^2^ [(1.96 + 0.84)]^2^ ÷ (4)^2^

n_1_ = n_2_ = 35

where Δ is |μ_2_ – μ_1_| (the absolute difference between two means), σ is the variance of two means, n_1_ is the sample size for group 1, n_2_ is the sample size for group 2, α is the probability of type 1 error (usually .05), β is the probability of type 2 error (usually .2), and z is the critical *Z* value for a given α or β.

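### The CARAT comparison ignores pre-treatment CARAT and lets a normality pretest choose the test, which costs efficiency and leaves the primary contrast unfixed

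*Protocol article*

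**What the plan says.** All from the protocol article.

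- **Primary Outcome Measure:** "The primary outcome measure is the mean change in the Control of Allergic Rhinitis and Asthma Test (CARAT) score", listed "at baseline and days 16, 31, 45, 75, 105, and 135". The scale runs from 0 to 30. No day is named as primary.
- **Sample Size:** for the Ayurvedic regimen, "a change of 14 points in the CARAT score was observed" in a pilot study. For the comparator, "it was assumed that a change of 10 points would be seen in the placebo group". The SD is given as "With an SD of 6 points based on the results of the previous pilot study", without saying whether it belongs to the change or to the score. The result is 35 per group, raised to 45 for 20% dropout.
- **Statistical Methods:** "When inferential analyses are conducted for continuous variables, they will be tested for normality. Nonparametric methods will be used for comparison of nonnormal data". For data judged normal, "between-group comparisons will be done using independent sample" t tests; otherwise the Mann-Whitney U test. No baseline covariate or adjusted model is mentioned. The normality test and its threshold are not given.
- **Table 1 (Study Procedure):** CARAT is ticked at screening and day 45 only. Whichever schedule holds, a pre-treatment CARAT value exists for each participant.

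**The concern.** The outcome and the sample size are framed as a difference in means. The t test addresses that difference; the Mann-Whitney U test compares ranks and does not estimate it. Under the stated rule, a preliminary test on the trial's own data settles which question the primary analysis answers. With several visits listed, different visits could end up with different tests.

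Separately, a change score subtracts baseline with a fixed coefficient of 1. ANCOVA estimates that coefficient and so usually leaves less residual variance. In randomized arms its treatment coefficient is still the difference in mean change, whether or not the data are normal. At stake are precision in a trial of 90 participants and, because the trial is open label, a primary test that can be shown to have been fixed in advance.

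**Working it through.** **Inputs.** From the protocol: difference 14 − 10 = 4 points, SD 6, two-sided 5%, 1:1 allocation, 35 per group, 20% dropout. Assumed, because the protocol does not give them: 6 is the SD of change; r, the correlation of pre-treatment and follow-up CARAT, is 0.3 to 0.7; k, the follow-up/baseline SD ratio, is 1 at first and then varied.

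**1. The protocol's own figure.** 2 × 6² × (1.96 + 0.84)² ÷ 4² = 35.28, stated as 35 (36 if rounded up). Allowing for dropout, 36 ÷ 0.8 = 45. The planned number is reproduced. Planned completers are 45 × 0.8 = 36 per arm, where the t test has 79.7% power. If all 45 per arm are analysed, power is about 88%.

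**2. ANCOVA with equal SDs.** With common SD s, Var(change) = 2s²(1 − r) and the ANCOVA residual variance is s²(1 − r²). The ratio is (1 + r)/2, so the residual SD is 6 × √((1 + r)/2).

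| r | variance ratio | residual SD | power, 36 per arm |
|---|---|---|---|
| t test on change | 1 | 6.00 | 79.7% |
| 0.3 | 0.65 | 4.84 | 93.3% |
| 0.5 | 0.75 | 5.20 | 89.6% |
| 0.7 | 0.85 | 5.53 | 85.7% |

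**3. ANCOVA with unequal SDs.** The ratio becomes k²(1 − r²) ÷ (1 + k² − 2rk).

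- r = 0.7, k = 1.2: 0.7344 ÷ 0.76 = 0.966; power 81%.
- r = 0.7, k = 1.4: 0.9996 ÷ 1.00 = 1.00; no gain.
- r = 0.7, k = 0.8: 0.3264 ÷ 0.52 = 0.628; power 94%.
- r = 0.3, k = 0.8: 0.5824 ÷ 1.16 = 0.502; power about 98%.

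The gain disappears when rk is near 1, because a coefficient of 1 on baseline is then the best one. Apart from the degree of freedom spent on the covariate, a correctly fitted ANCOVA is not expected to fall materially below the t test on change.

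**4. If 6 is the SD of the score instead (k = 1, 35 per arm, normal approximation).** The change-score t test has 65%, 80% and 95% power at r = 0.3, 0.5 and 0.7; ANCOVA has 83%, 90% and 97%.

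**5. The pretest procedure by simulation.** 3,000 runs per setting, 35 per arm, Shapiro-Wilk in each arm at 5% (an assumption, since the protocol names no test), then a t test or Mann-Whitney on change, against ANCOVA.

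| Data | Pretest procedure, r = 0.3 / 0.5 / 0.7 | ANCOVA |
|---|---|---|
| Normal | 79 / 78 / 77% | 92 / 88 / 83% |
| Rounded and clipped to 0–30, assumed baseline mean 12 | 72 / 68 / 62% | 91 / 86 / 77% |

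With truly normal data, about 10% of trials were still switched to Mann-Whitney. Type I error was about 5% for both procedures in every setting. The ANCOVA coefficient matched the difference in mean change throughout (for example 4.0 and 4.0 with normal data, 3.5 and 3.5 with clipped data).

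**The case against.** A t test on change between randomized arms is valid, and it matches the two-means formula used for the sample size. The section is a general paragraph for all continuous variables in a condensed article, and covariate adjustment is often left to an SAP, which is not shown. Both observations are fair. But the article does more than stay silent: it names the tests and the rule for choosing between them, and offers nothing else for the primary outcome.

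A reader might infer that unadjusted change scores bias the result through regression to the mean or chance imbalance. The documents do not support that. Under 1:1 randomization both arms regress alike in expectation, and the standard error already covers chance imbalance.

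A reader might also infer that the trial has no power to spare. The 80% is what remains after the allowed dropout; with all 45 per arm analysed it is about 88%.

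Nor is ANCOVA always the more powerful choice. With very heavy-tailed errors (t with 3 degrees of freedom) and r = 0.7, the pretest procedure reached 92% against 87%. Such tails are implausible on a bounded 0–30 score, but the example rules out a universal claim. The size of the gain also rests on r, k and the meaning of the SD, none of which the protocol gives.

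**Conclusion.** The point holds as one of efficiency and of an unfixed target. The protocol defines and sizes its primary outcome as a difference in mean CARAT change, then lets a pretest decide whether that difference is what is tested, and it leaves the pre-treatment score out of the comparison. It does not hold as a claim of bias or of inflated type I error.

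The power figures are illustrative. The rise from 80% to 86–93% at 36 per arm needs 6 to be the SD of change, equal SDs, and r between 0.3 and 0.7. Letting the SD ratio run from 0.8 to 1.4 widens the result to anything from no gain to about 98%. What does not depend on those assumptions is that ANCOVA fixes the contrast in advance as the stated mean difference.

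**What to change.** By dated amendment, before outcome data are analysed:

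1. Make the primary analysis ANCOVA of follow-up CARAT on treatment and pre-treatment CARAT, reporting the adjusted mean difference with its 95% CI and robust standard errors.
2. Remove the normality gate for the primary outcome and keep Mann-Whitney as a sensitivity analysis.
3. Name the covariate value. The outcome section says baseline and Table 1 ticks screening, so the two must be reconciled.
4. Name the primary visit and state it openly as a choice. Day 45 is the only follow-up visit on which the outcome section and Table 1 agree.

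The cost is a short amendment and one regression command in the Stata version already named, with no extra participants, visits or data. Timing is the one constraint: 72 participants were enrolled by May 2024 and analysis was due by February 2025, so in an open-label trial the amendment's date relative to any look at outcome data must be on record.

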### Ethical Considerations

This research protocol has been reviewed and approved by the Institutional Ethics Committee of Vardhman Mahavir Medical College, Safdarjung Hospital, New Delhi (IEC/VMMC/SJH/Project/2023-02/cc-320 dated 28.03.2023). Participants will receive an information sheet with the research details given in two languages (Hindi and English). Voluntary signed informed consent will be obtained from the participants before any clinical trial–related procedure. The participants will be informed by the investigator that all trial data recorded will be treated in strict confidence. During documentation and analysis of the trial, the individual participant will only be identified by their enrollment number.

Participant confidentiality will be guaranteed, and only researchers will have access to the data. Participants are nominally compensated for their loss of wages and conveyance charges by paying an amount of ₹100 (US $1.19) for every visit to the hospital during the study period. The safety of the trial intervention will be evaluated by recording the incidence of adverse events on every scheduled follow-up visit. All adverse events during the study timeline will be recorded and monitored per the International Council for Harmonisation of Technical Requirements for Pharmaceuticals for Human Use and Guideline for Good Clinical Practice guidelines. The investigator will report the same to the institutional ethics committee and the sponsors as soon as possible.

For facilitating appropriate reference standards for scientific, ethical, and safety issues before the trial begins, this protocol has been developed according to the 2013 SPIRIT (Standard Protocol Items: Recommendations for Interventional Trials) and CONSORT (Consolidated Standards of Reporting Trials) statements.

### Data Safety and Monitoring

After 25% of the participants complete the study, the data will be analyzed for the trial drugs’ safety. The project monitoring committee will monitor the trial’s progress through review meetings and site visits as per the requirement for ensuring strict adherence to the trial protocol and accurate completion of the CRFs.

### Drug Compliance

The compliance of taking trial drugs will be assessed at each visit during the follow-up visits (days 16, 31, 45, and 75) by assessing the approximate quantity consumed. The participants with ≥80% compliance will continue the study.

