### Study Interventions (Investigational Products)

Participants in the treatment group will undergo Nasya therapy for 7 days for 3 consecutive cycles. Along with the Nasya therapy, the participants will receive a 250 mg dose of NLR twice daily after meals with lukewarm water and 40 ml of Shirishadi Kwath twice daily on an empty stomach for 45 days. In the standard control group, participants will receive a 200 mcg dose of fluticasone propionate nasal spray (50 mcg/spray) per day (2 puffs once daily) for 45 days. The treatment group medicine (investigational products) will be procured from good manufacturing practice–certified pharmacies through the Indian Medicines Pharmaceutical Corporation Limited (Mohaan) and the Central Ayurveda Research Institute (Jhansi), along with a certificate of analysis to ensure the investigational products’ quality standards and safety. The control group’s medicine will be procured from a good manufacturing practice–certified government agency. The study drugs will be kept in a secure place and will only be supplied to the participants under the guidance of the investigator. A record will be maintained for the drug dispensed. Any discrepancies between the amounts dispensed and returned will be explained.

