### Strategies to Improve Adherence to the Study Protocol

Medication adherence will be assessed at each follow-up visit (days 16, 31, 45, 75, 105, and 135) by assessing the approximate quantity consumed. The participant will be asked to return the empty medicine container at each follow-up visit. Repeated phone reminders to regularly take the medicine from project staff will be given to the participants or their family members.

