### Data Collection, Management, and Analysis

The data collection will include all information in the CRFs. All participants will be assigned an enrollment number, which will be used for CRFs and electronic databases. Consent forms and CRFs will be stored in locked cupboards, and electronic databases will be password protected. The data will be entered using the double-entry method for accuracy. All data will be accessible to the principal investigator and coinvestigators during and after the study, and will be available to sponsors and monitors as required. Data will be stored for 5 years and then destroyed. In case of dropout, 10% of the data will be inserted through the imputation technique. Proper documentation will be done to ensure accurate interpretation and verification related to the study. The analysis will be done by the CCRAS statistical unit. If any participants withdraw from the study prematurely, an attempt will be made to collect data for at least 1 month after enrollment, which includes the objective clinical and laboratory results. Data are important to the integrity of the final study analysis since early withdrawal could be related to the study drug’s safety profile.

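### The 80% compliance rule, read literally, ends study participation on post-randomization behaviour; this undermines the promised intention-to-treat analysis and creates a risk of bias of unknown size and direction

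*Protocol article*

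**What the plan says.** All places are in the protocol article.

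- **Drug Compliance:** compliance is checked at "follow-up visits (days 16, 31, 45, and 75) by assessing the approximate quantity consumed", and then "The participants with ≥80% compliance will continue the study". The section does not spell out what happens below 80%.
- **Statistical Methods:** "Per-protocol and intention-to-treat analyses will be carried out at the end of the study". No section ties the 80% threshold to the per-protocol set.
- **Data Collection, Management, and Analysis:** for premature withdrawals, "an attempt will be made to collect data for at least 1 month after enrollment", covering objective clinical and laboratory results. Also, "In case of dropout, 10% of the data will be inserted through the imputation technique".
- **Primary Outcome Measure:** change in CARAT, measured "at baseline and days 16, 31, 45, 75, 105, and 135". Table 1 ticks CARAT only at screening and day 45.
- **Study Interventions:** the Ayurvedic arm has Nasya in three 7-day cycles, NLR twice daily after meals, and "40 ml of Shirishadi Kwath twice daily on an empty stomach for 45 days". The control arm has one nasal spray product once daily for 45 days.
- **Strategies to Improve Adherence:** a longer list of compliance visits ("Medication adherence will be assessed at each follow-up visit (days 16, 31, 45, 75, 105, and 135") with no continuation rule. Table 1 ticks drug compliance only at days 16, 31 and 45.

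**The concern.** An intention-to-treat comparison needs outcomes on everyone randomized. A rule that lets compliance decide who stays makes outcome data depend on behaviour after randomization, and that behaviour can reflect tolerability or response. The trial is open label and one regimen is far more demanding than the other, so removal may differ between arms and may relate to outcome. If both happen, the patients who remain are no longer comparable groups. The article itself notes, in its data-collection section, that early withdrawal may be connected with drug safety. Outcomes that were never collected cannot be recovered at analysis.

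**Working it through.** **1. The plan's own figure.** Inputs from Sample Size: difference 4 points (14 minus 10), SD 6, two-sided α 0.05, power 80%.

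n per arm = 2 × 6² × (1.96 + 0.84)² ÷ 4² = 35.28. The plan states 35. With 20% dropout, 35.28 ÷ 0.80 = 44.1, rounded up to 45, as stated. The plan's figures reproduce within rounding.

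**2. Can the rule mean only that study medicine stops?** Treatment lasts 45 days. The section's own list of checks includes day 75, when no study medicine remains to be stopped. Even the day 45 check, the last one in Table 1, falls at the end of treatment. The wording also refers to continuing the study, not the medicine. The natural reading is that follow-up ends.

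**3. What would be in hand for someone removed.** This assumes that the outcomes due at a visit are taken before the patient leaves.

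| First found below 80% | CARAT in hand, Primary Outcome Measure schedule | CARAT in hand, Table 1 schedule |
|---|---|---|
| Day 16 | baseline, 16 | screening only |
| Day 31 | baseline, 16, 31 | screening only |
| Day 45 | baseline, 16, 31, 45 | screening, 45 |
| Day 75 | baseline, 16, 31, 45, 75 | screening, 45 |

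The 1-month minimum after withdrawal reaches about day 30, before day 45 and well before day 135. It names objective clinical and laboratory results, so CARAT, a patient questionnaire, is not clearly covered. The 10% imputation provision is half of the 20% dropout assumed for the sample size.

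**4. Illustration of bias.** The documents give no non-compliance rate and no outcome by compliance, so the removal shares and gaps here are assumptions. Setting: no true difference, 45 per arm, SD 6, only retained patients analysed, and removed patients' mean improvement g points below that of the others in both arms.

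A retained mean exceeds its arm's full mean by (share removed) × g, so

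bias = (share removed, Ayurvedic − share removed, control) × g

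SE = 6 × √(1/n₁ + 1/n₂), and type I error = P(|Z + bias/SE| > 1.96).

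| Removed (Ayurvedic vs control) | g | Retained | Bias | SE | Type I error |
|---|---|---|---|---|---|
| 10% vs 10% | any | 40.5, 40.5 | 0 | 1.33 | 5.0% |
| any | 0 | – | 0 | – | 5.0% |
| 20% vs 5% | 3 | 36, 43 | 0.15 × 3 = 0.45 | 1.36 | 6.3% |
| 20% vs 5% | 5 | 36, 43 | 0.15 × 5 = 0.75 | 1.36 | 8.6% |
| 30% vs 10% | 5 | 31.5, 40.5 | 0.20 × 5 = 1.0 | 1.43 | 10.8% |

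Against the planned 4 points, 0.45 to 0.75 is 11% to 19%, and 1.0 is 25%. If removed patients would have done better than the rest (g negative), the bias has the same size and the opposite sign.

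**5. Power.** With 36 per arm (45 × 0.80), power for 4 points is 80.7%. If compliance removals came on top of the 20% dropout, power would be 76.5% with a further 10% removed (32.4 per arm) and 71.6% with a further 20% (28.8 per arm). The documents do not say whether the 20% already includes such removals.

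**The case against.** The strongest reply is that the article does provide for early leavers. It plans an attempt at data collection after withdrawal and some imputation. Compliance is also checked at visits where outcomes are taken, so a patient first found below 80% at day 45 or 75 already has end-of-treatment CARAT and endoscopy. The consequence of falling below 80% is an inference, because the section states only who continues.

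Much of this stands, and it rules out several stronger readings that a reader might infer:

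- *Intention-to-treat is impossible.* Not supported: it can be attempted, partly on imputed values.
- *Every low complier's outcome is lost.* Not supported: all post-baseline CARAT is missing only for removal at day 16 or 31 under the Table 1 schedule, and only if nothing is collected after withdrawal.
- *The comparison is biased in favour of the Ayurvedic arm.* Not supported: the documents show unequal burden, not who would be removed. Patients may also stop because they feel well, which would reverse the direction.
- *The rule uses up the 20% dropout allowance.* Not supported: the article does not say what the 20% covers.

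The reply does not remove the conflict. The post-withdrawal minimum ends before the end of treatment, CARAT is not clearly included in it, and a continuation rule applied at day 75 cannot be only about medicine.

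**Conclusion.** The point holds as an inconsistency that weakens the primary comparison. The compliance rule, read literally, ends participation on post-randomization behaviour. The withdrawal and imputation provisions only partly make good the intention-to-treat analysis that the article promises. Later outcomes for those removed would be missing or imputed, with the worst case at days 16 and 31.

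Bias is a risk, not an established fact. It needs removal related to outcome and differing between arms, or removed patients who differ in kind between arms. The illustrated range runs from no bias to 1.0 CARAT point and a type I error of about 11%, and it rests wholly on assumed removal shares and outcome gaps. Confidence is high on the conflict between the sections and low on the size or direction of any bias.

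**What to change.** Reconcile Drug Compliance, Data Collection, and Statistical Methods. Suggested wording: *Compliance of at least 80% defines the per-protocol set only. Every randomized participant remains in scheduled outcome follow-up to day 135, with CARAT collected whatever the compliance, and all are included in the intention-to-treat analysis.*

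In the same amendment:

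- replace the 1-month minimum for data collection after withdrawal with follow-up to day 135, and state that CARAT is included;
- align the CARAT visits in Table 1 with the Primary Outcome Measure section;
- reconcile the three differing lists of compliance visits;
- try to recall anyone already removed for low compliance for their remaining visits. The article reports 72 enrolled by May 2024, so this should be done promptly.

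The cost is a short amendment, a note to the site, and some extra attendance at visits already on the schedule. No additional patients are needed. Whether study medicine continues below 80% is a clinical matter and is not addressed here.
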